## **1. Background:**

Implantation of a pacemaker is the treatment of choice for bradyarrhythmias. The short- and long-term success of permanent pacing is critically dependent on a stable position of the electrode. Historically, the first pacing electrodes were lacking mechanisms for fixation and therefore were associated with an unacceptably high risk of dislodgement. With the development of passive and active myocardial fixation mechanisms for electrodes the need for lead repositioning has been dramatically reduced (1).

Passive fixation leads are typically equipped with small plastic tines that entrap within the trabeculae of the right heart chambers immediately upon correct positioning of the lead. For active fixation leads different fixation mechanisms (screws, barbs or hooks) have been developed, but active screws represent the most frequently used type (2,3,4).

Both lead types encounter their own specific advantages and disadvantages.

Passive fixation electrodes show less pronounced electric injury currents during implantation and therefore judgement of the appropriate lead position and the pacing and sensing capabilities are facilitated. They can be easily used in a typical right ventricular apical lead position but are not deemed to be ideal for alternate pacing locations such as the right ventricular mid septum, the outflow tract or the his bundle region. Passive fixation leads are rapidly covered by fibrous tissue, making later removal of the lead by simple traction more difficult.

Active fixation leads with an extendable and retractable screw design are widely used for their ease of implantation irrespective of the final lead position in the heart. Advantages during lead revisions include the ability to retract the screw even years after implantation and thus allow easier extraction procedures (3). Disadvantages of active fixation leads mainly include a trend to slightly higher rates of perforation during implantation (5). Additionally, there is a belief that active fixation electrodes may be more aggressive to the myocardium during implantation and that they could cause a more pronounced myocardial micro-damage on implantation.

Because the stimulation thresholds of active and passive fixation leads tend to be similar, and differences in the rate of lead dislodgement and perforation are marginal (trend towards superiority of active fixation leads in the first and passive fixation leads for the latter), the choice of an active or a passive ventricular fixation electrode is largely a matter of personal

preference of the implanting physician (4). This is especially true for the right ventricular apical lead position which encounters >90% of ventricular lead positions.

Bearing in mind the equal performance of both lead types, the ability to implant the electrode as atraumatic as possible has come into the focus for electrode selection. Transvenous insertion of either passive or active endocardial leads for permanent pacing is accompanied by troponin elevation compatible with myocardial damage, secondary to the direct myocardial trauma elicited by pacing leads. Published data mostly report troponin elevations within or very close to the range of “minimal myocardial damage” (6,7,8) but usually did not exceed 3 ng/ml (9). These cardiac troponin-I (CTN-I) elevations occurred within 6 h after implantation (6).

Although active fixation leads are thought to be potentially more traumatic and therefore may be correlated with a higher troponin release, no randomized trial has been conducted to evaluate myocardial micro-damage with respect to different electrode types.

Therefore the primary aim of the PACMAN trial is to investigate whether ventricular active or passive fixation electrodes are associated with a different amount of myocardial micro-damage which is reflected by potentially different levels of high-sensitivity troponin release after pacemaker implantation.

## **2. Hypothesis:**

The implantation of a pacemaker system is associated with an increase in the plasma concentrations of the high-sensitivity troponin T which serves as a surrogate for myocardial damage. The increase in plasma concentrations of high-sensitivity troponin T is not related to the use of an active or a passive fixation of the ventricular lead.

## **3. Study design:**

The PACMAN trial is designed as a prospective randomised, multi-centre, international study.

## **4. Inclusion and exclusion criteria:**

### **Inclusion**

- Indication of de-novo (single or dual chamber) pacemaker implantation according to current national or international guidelines

Or

- Additional ventricular lead insertion on the occasion of lead revisions with no explantation attempt for abandoned leads

### **Exclusion**

- Cardiac resynchronisation therapy or AAI pacing
- Revision (except for adding a ventricular lead to pre-existing leads)
- Temporary pacing
- ICD indication
- Right ventricular pacing aimed from the mid-septum, outflow tract or his bundle region
- Severe tricuspid regurgitation requiring active fixation leads
- Planned cardioversion during pacemaker implantation or within 24 hours thereafter
- NYHA IV
- (Cardiogenic) shock
- Heart Surgery, acute coronary syndrome, myocardial infarction, any revascularisation, cardioversion or ablation procedure within the last 4 weeks with elevated base line high-sensitivity troponin levels.
- Pulmonary embolism, stroke, dialysis within the last 4 weeks
- Patient not available for follow-up
- Patient's inability to consent or refusal to consent
- Age <18 years, pregnancy

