### **5. Study procedure:**

After obtaining written informed consent to the pacemaker implantation and the study participation the baseline high-sensitivity troponin T plasma concentration will be determined. This will be done from a previously taken blood sample provided for standard clinical tests if the sample is not older than 24 hours. If no such sample is available or if retrospective analysis is not possible an additional blood sample is required. Prior to pacemaker implantation the patient will be randomly assigned to receive a CE-marketed, commercially available, ventricular passive or active fixation electrode. Randomisation will be stratified for single- and dual-chamber pacing and for centres in a 1:1 ratio between active fixation and passive fixation leads for right ventricular pacing; for atrial leads active fixation will be used. The randomisation will be performed in varying blocks for each of stratify and will be centrally generated in the Deutsche Herzzentrum München. The participating centres will be provided with sealed envelopes containing the randomisation information. During pacemaker

implantation all necessary – and clinically reasonable - efforts should be made to adhere to the randomised lead type. Cross-overs (to avoid unsuccessful pacemaker implantations) will be allowed on the basis of the individual judgement of the implanter. In case of cross-over, the primary endpoint will be evaluated on an intention-to-treat basis. After pacemaker implantation, the patient will be followed according to standard clinical practice. Standard clinical practice includes the drawing of blood samples post-implantation (usually the next morning). For study reasons this should be done between 6 and 24 hours after pacemaker implantation. On this occasion, additionally to the routine parameters, high-sensitivity troponin T plasma concentration will be determined. The patients will be followed for three months with respect to lead performance, necessity of lead revision and mortality.

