## **6. Endpoints:**

### **Primary endpoint:**

The primary endpoint is based on the comparison of the increase of high-sensitivity troponin T plasma concentrations (measured with Roche hs-TropT assay; difference between post-implantation and pre-implantation concentrations) between patients receiving a passive fixation or an active fixation ventricular electrode.

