## **9. Statistics**

Because there is no data available on high-sensitivity troponin T release after pacemaker implantation, historic data from patients supplied with pacemakers in the German Heart Centre 2011 were used for sample size calculation. For this, data of the most recent 30 patients (most recent 15 patients with active fixation ventricular leads and most recent 15 patients with passive fixation ventricular leads) with available high-sensitivity troponin T levels before and after pacemaker implantation were analysed. They did not differ relevantly in their baseline

characteristics and the distribution of high-sensitivity troponin T plasma concentrations is shown in the following table.

[figure not shown]

A=active fixation; P=passive fixation;

delta.hsTroponin refers to change plasma concentrations measured in ng/ml

The distribution is non-normal and due to large variations in the values including negative increases of plasma concentration after pacemaker implantation a non-parametric test (Mann-Whitney U Test) is the most appropriate approach to sample size estimation.

Null hypothesis: The probability that a randomly selected patient of the study cohort who received an active fixation ventricular pacemaker electrode shows a larger increase of high-sensitivity troponin T after implantation than a randomly selected patient who received a passive fixation ventricular pacemaker lead is 50 %.  $H_0: P(A > P) = P(P > A) = 50\%$ .

In the cohort of historic patients from the German Heart Centre the above mentioned probability was  $P(A > P) = 59\%$ . For sample size calculation it was assumed that an effect of  $P(A > P) = 60\%$  or  $P(P > A) = 60\%$  would determine the least difference that would be considered as clinically relevant..

Assuming that there is a relevant difference between both groups, a total of 262 patients need to be recruited (131 patients per group) to find a significant effect with a probability (=power) of at least 80% on a two-sided level of significance of  $\alpha=5\%$  (10).

Assuming a drop-out rate of 10% for this acute study, a total of 290 patients (145 patients per group) will be enrolled in the study.

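### Only planned cardioversion is barred in the troponin sampling window, so another planned troponin-relevant procedure stays eligible and dilutes the primary comparison

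*Protocol*

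**What the plan says.** Four places in the protocol matter here.

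- **Section 4, Exclusion, looking forward:** the only procedure named is cardioversion: "Planned cardioversion during pacemaker implantation or within 24 hours thereafter".
- **Section 4, Exclusion, looking back:** a separate line lists heart surgery and acute coronary events and continues with "any revascularisation, cardioversion or ablation procedure within the last 4 weeks with elevated base line high-sensitivity troponin levels".
- **Section 5, Study procedure:** on the baseline troponin value, "This will be done from a previously taken blood sample provided for standard clinical tests if the sample is not older than 24 hours"; an extra sample is drawn where no usable one exists. On the post-implantation sample, "For study reasons this should be done between 6 and 24 hours after pacemaker implantation".
- **Section 6, Primary endpoint:** the outcome is the plain "difference between post-implantation and pre-implantation concentrations", with no separate handling of patients who have another cardiac procedure between the two samples. Section 2 describes the marker as "high-sensitivity troponin T which serves as a surrogate for myocardial damage".

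**The concern.** The two exclusion lines do not match. Looking back, four kinds of procedure (heart surgery, revascularisation, cardioversion, ablation) are treated as able to disturb troponin. Looking forward, over a period that ends when the sampling window ends, only one of them is. Under the text as written, a patient with an ablation, revascularisation or heart operation planned in the same session, or before the post-implantation sample, meets every criterion.

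There is a second, narrower route. The backward line depends on a raised baseline value, and that value may come from a sample up to 24 hours old. If a procedure took place after that sample but before implantation, the baseline can be normal. The patient is then eligible, and the release from that procedure falls between the two measurements.

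In either case the change score contains troponin that the ventricular lead did not cause. The primary comparison works on ranks, so such a patient's rank may say little about the lead type. The secondary endpoint on reaching the troponin threshold is exposed in the same way.

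**Working it through.** **1. Does anything else in the protocol close the gap?** The remaining exclusions in section 4 concern device type, lead position, temporary pacing, clinical state, pulmonary embolism, stroke, dialysis, consent, follow-up, age and pregnancy. None names a planned ablation, revascularisation or heart operation. Section 5 allows cross-over of lead type and keeps those patients by intention to treat, but does not mention concomitant procedures. The gap stays open.

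**2. How the backward line is read.** The raised-baseline condition may apply to the whole list or only to the procedure named last. On the second reading the stored-sample route remains for ablation only. The forward gap does not depend on the reading.

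**3. The plan's own sample size.** Inputs from section 9: P(A>P) = 0.60, two-sided α = 5%, power 80%, equal groups, Noether's formula.

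N = (1.960 + 0.842)² / [12 × 0.5 × 0.5 × (0.60 − 0.50)²] = 261.6, rounded up to 262. This matches the protocol.

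Power at N = 262 is Φ(√(3 × 262) × 0.10 − 1.96) = Φ(2.804 − 1.96) = 80.1%.

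**4. Dilution.** Assumptions, none of them from the protocol: a share f of each arm has such a procedure between the samples; each affected patient outranks every unaffected one; the lead effect among unaffected patients is 0.60.

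Taking one patient from each arm:
- both unaffected, probability (1 − f)²: A exceeds P with probability 0.60
- only A affected, probability f(1 − f): A exceeds P
- only P affected, probability f(1 − f): P exceeds A
- both affected, probability f²: 0.50

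Summing, P(A>P) = 0.60(1 − f)² + f(1 − f) + 0.50f² = 0.5 + 0.1(1 − f)².

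| f | P(A>P) | Power at 262 | N for 80% |
|---|---|---|---|
| 0 | 0.600 | 80.1% | 262 |
| 1% | 0.598 | 78.5% | 273 |
| 2% | 0.596 | 76.8% | 284 |
| 5% | 0.590 | 71.6% | 322 |

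**5. Between-arm effect.** Section 5 states "Randomisation will be stratified for single- and dual-chamber pacing and for centres in a 1:1 ratio". A procedure planned or done before randomisation is therefore spread over the arms by chance. With no lead effect, the change scores are exchangeable between arms, with or without affected patients, so the Mann-Whitney test keeps its 5% level.

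**The case against.** **No bias between arms.** A reader might infer that a chance imbalance in affected patients creates a spurious lead effect. With shares of 5% and 2% and no lead effect, the AUC would be 0.05 × 0.98 + 0.5 × (0.95 × 0.98 + 0.05 × 0.02) = 0.515. The null standard error is 1/√786 = 0.036, so this shift is 0.015/0.036 = 0.42 standard errors. That is ordinary sampling variation, already covered by the test level. The objection stands, and only dilution remains.

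**The size is undocumented.** Nothing in the protocol says how often such procedures coincide with implantation, and the stored-sample route needs several events within about a day. Having every affected patient outrank all others is a worst case. This also stands: at f = 1% the loss is under two percentage points.

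**The 0.60 may already include dilution.** Section 9 derives its planning from recent routine patients, in whom P(A>P) was 59%, and does not say that patients with other procedures were removed. It then takes 60% as the effect that "would determine the least difference that would be considered as clinically relevant". If 0.60 was meant for a population that includes such patients, the loss in the table is partly counted twice. The figures hold only if 0.60 describes the effect of the lead alone.

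**A broad exclusion could do harm.** Barring every procedure performed between the samples would remove patients after randomisation, for instance one operated on for a perforation. Section 1 reports a trend to more perforations with active fixation, so such removal could depend on the arm. This stands and limits the fix to what is planned at enrolment.

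None of these points removes the mismatch between the two exclusion lines.

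**Conclusion.** The gap in the eligibility wording is certain from the text; its effect on the trial is probably modest and cannot be fixed from the protocol. Under the worst-case ranking, power falls from 80% to about 78.5%, 77% or 72% for f of 1%, 2% or 5%. The protocol supports no particular value of f.

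The text does not support reading this as systematic bias or as an inflated type I error. The dilution is still not harmless in this trial. Section 2 hypothesises that the rise is unrelated to lead type, and a pull of the AUC toward 0.5 leans toward that hypothesis.

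A reader might go further and infer that dilution by itself delivers the non-inferiority conclusion in section 9. It does not: at an AUC of 0.50 with 262 patients, the lower 95% limit is about 0.50 − 1.96 × 0.036 = 0.43, below the required 0.45.

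The point is worth acting on because the remedy is cheap, not because a large loss has been shown.

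**What to change.** Reconcile the two exclusion lines in section 4 with each other and with the sampling times in section 5.

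1. Extend the forward-looking exclusion to any cardioversion, ablation, revascularisation or heart surgery that, at enrolment, is planned to take place before the post-implantation troponin sample.
2. Add a sentence to section 5: the baseline sample must have been drawn after any such procedure done before implantation; otherwise the additional sample already foreseen there is taken. The four-week criterion is then applied to a baseline that follows the procedure.
3. State that unplanned procedures after randomisation are not grounds for exclusion. Record type and time, and keep the patients in the intention-to-treat analysis.

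The change concerns only who enters and which sample counts as baseline, not whether or when a procedure is clinically indicated. It costs one amended exclusion line, a short addition to section 5 and a field on the case report form. A few patients are excluded or need the extra 2 ml of blood that section 7 already describes. The planned sample size does not change.

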### **5. Study procedure:**

After obtaining written informed consent to the pacemaker implantation and the study participation the baseline high-sensitivity troponin T plasma concentration will be determined. This will be done from a previously taken blood sample provided for standard clinical tests if the sample is not older than 24 hours. If no such sample is available or if retrospective analysis is not possible an additional blood sample is required. Prior to pacemaker implantation the patient will be randomly assigned to receive a CE-marketed, commercially available, ventricular passive or active fixation electrode. Randomisation will be stratified for single- and dual-chamber pacing and for centres in a 1:1 ratio between active fixation and passive fixation leads for right ventricular pacing; for atrial leads active fixation will be used. The randomisation will be performed in varying blocks for each of stratify and will be centrally generated in the Deutsche Herzzentrum München. The participating centres will be provided with sealed envelopes containing the randomisation information. During pacemaker

implantation all necessary – and clinically reasonable - efforts should be made to adhere to the randomised lead type. Cross-overs (to avoid unsuccessful pacemaker implantations) will be allowed on the basis of the individual judgement of the implanter. In case of cross-over, the primary endpoint will be evaluated on an intention-to-treat basis. After pacemaker implantation, the patient will be followed according to standard clinical practice. Standard clinical practice includes the drawing of blood samples post-implantation (usually the next morning). For study reasons this should be done between 6 and 24 hours after pacemaker implantation. On this occasion, additionally to the routine parameters, high-sensitivity troponin T plasma concentration will be determined. The patients will be followed for three months with respect to lead performance, necessity of lead revision and mortality.

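### Allocation concealment is not secured: assignments are held at the implanting centres in sealed envelopes, and nothing requires registration and locked eligibility before an envelope is opened

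*Protocol*

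**What the plan says.** Protocol Section 5 (Study procedure) fixes the allocation method:

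- **Strata and ratio:** "Randomisation will be stratified for single- and dual-chamber pacing and for centres in a 1:1 ratio".
- **List:** "The randomisation will be performed in varying blocks for each of stratify and will be centrally generated". Block sizes are not given.
- **Where the assignments are kept:** "The participating centres will be provided with sealed envelopes containing the randomisation information".
- **Order of events:** "After obtaining written informed consent to the pacemaker implantation and the study participation the baseline high-sensitivity troponin T plasma concentration will be determined". Assignment follows, at some time before implantation.

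The text reviewed does not say whether the envelopes are opaque or numbered, who keeps or opens them, whether opening is recorded, or whether the patient must be registered with eligibility complete before opening. Sections 8 and 11 were not in that text.

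Two exclusions in Section 4 bear on lead type: "Right ventricular pacing aimed from the mid-septum, outflow tract or his bundle region" and "Severe tricuspid regurgitation requiring active fixation leads". No blinding is described. Section 1 states that "the choice of an active or a passive ventricular fixation electrode is largely a matter of personal" preference of the implanting physician.

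**The concern.** Concealment means that nobody deciding whether to enter a patient can know the next assignment. Here the assignment lies in the same building as the person who decides, and that person cannot be blinded to the lead. Section 1 supplies both a preference and a possible motive: lead choice is described as personal, and active fixation is said to be believed more traumatic.

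An implanter who had seen the next assignment could use the two exclusions in either direction. Before a passive assignment, regurgitation could be judged to need active fixation. Before an active one, a septal position could be declared as the target.

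The primary endpoint is a laboratory value, so biased assessment is a small worry and selection at entry is the main route for bias. If patients with a larger expected release were kept out of one arm, P(A > P) would move away from 50% without any lead effect. That affects the Mann-Whitney test and also the Section 9 fallback, which asks whether the lower 95% limit of the AUC exceeds 0.45.

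**Working it through.** **1. The plan's own figure.** By Noether's formula with p = 0.60, equal arms, two-sided 5% and 80% power: N = (1.960 + 0.842)² / [12 × 0.25 × (0.60 − 0.50)²] = 7.849 / 0.03 = 261.6, so 262 (131 per arm). This agrees with Section 9. The point raised here does not change it.

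**2. What the text protects against, and what it does not.**

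| Element of Section 5 | Protects against | Leaves open |
|---|---|---|
| Central list | Sites constructing the sequence | Sites holding the assignments |
| Varying blocks | Certain prediction from past assignments | Reading the assignment itself |
| Sealed envelopes | Casual sight | Early or out-of-order opening, because no log or numbering is stated |
| Consent and baseline sample first | Assignment before consent | Eligibility settled after opening |
| Intention to treat for cross-overs | Bias from changes after assignment | Selection before entry |

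**3. Guessing without opening.** Block sizes are an assumption. Guessing the under-represented arm within a stratum is right about 72% of the time with sizes 2/4, 69% with 4/6 and 67% to 68% with 4/6/8, against 50% by chance. Central release does not remove this part. It removes the possibility of reading the assignment.

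**4. Illustration of size (all inputs assumed).** Expected release x and actual release y have correlation ρ, there is no true lead effect, and there are 131 patients per arm. Patients in the top quarter of x are diverted from the active arm with probability d and replaced by the next patient.

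The standard error of the AUC under the null is √[(262 + 1) / (12 × 131²)] = √(263 / 205,932) = 0.0357.

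For d = 50%, which removes 0.50 × 0.25 = 12.5% of active-arm candidates:

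| ρ | Simulated mean AUC | Shift / SE | Rejection by normal approximation | Simulated rejection |
|---|---|---|---|---|
| 0.3 | 0.484 | 0.016 / 0.0357 = 0.45 | 7% | 7% |
| 0.5 | 0.474 | 0.026 / 0.0357 = 0.73 | 11% | 11% |
| 0.7 | 0.463 | 0.037 / 0.0357 = 1.04 | 18% | 18–19% |

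The approximation is Φ(−1.96 + shift/SE) + Φ(−1.96 − shift/SE).

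Other simulated settings, over the same range of ρ:
- d = 10%: about 5% to 6%.
- d = 25%: 5% to 8%.
- d = 100%: 17–18%, 40% and 67–68%.
- Selection confined to the top 5%, half of them diverted: 5% to 6%.

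**5. The fallback.** With the null standard error, the lower limit exceeds 0.45 when the AUC exceeds 0.45 + 1.96 × 0.0357 = 0.520.
- No bias: Φ((0.500 − 0.520) / 0.0357) = 29% in either direction.
- d = 50%, ρ = 0.5, direction favouring active leads (AUC 0.526): Φ(0.006 / 0.0357) = 57%.
- Same setting, other direction (AUC 0.474): Φ(−0.046 / 0.0357) = 10%.

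A shift of 0.026 uses up about half of the 0.05 margin (0.026 / 0.05 = 52%).

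**The case against.** The case on the other side is substantial.

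- **The envelopes are sealed.** With a central list and varying blocks this is a recognised concealment method, and silence about early opening is not permission. This stands. A reader might infer that the implanter knows the next lead type. The text does not support that, because foreknowledge needs a breach or an early opening.
- **Most exclusions are clinical or administrative facts.** This also stands. A reader might infer that eligibility in general depends on the implanter's view. Only two criteria leave that room, and one of them also requires the regurgitation to be severe. Section 5 does refer to the implanter's individual judgement, but about cross-over after assignment, not about entry.
- **Cross-over is an outlet, and all centres are experienced with both leads (Section 7).** This weakens the motive but does not remove it. Section 5 permits cross-over to avoid a failed implantation and otherwise asks for adherence, so it is not a route for plain preference.
- **The simulation is one-directional and selects on expected release.** This stands. The two exclusions could be used in opposite directions and are not defined by expected release. Section 9 says no data on high-sensitivity troponin T release after implantation were available, so no correlation can be justified from the document.
- **A sentence on envelope handling might suffice.** Partly accepted. It would close most of the gap and is kept as the back-up, but the assignments would still be on site.

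**Conclusion.** Concealment is not secured. The protocol places the assignments with the centres and does not tie opening an envelope to irrevocable entry of a patient already found eligible. The implanter must know the lead, and two exclusions give room for a decision linked to it. Selection at that stage would bias both the primary comparison and the fallback, and no analysis can restore what was lost. Allocation handling has to be settled before the first patient, so it belongs in the protocol rather than in the SAP.

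The document shows a weakness, not a breach, and the size of any bias cannot be derived from it. The illustrated error rates rest wholly on assumed diversion and correlation. They stay near 5% at modest diversion, and the highest need every top-quarter patient to be diverted. They should not be cited as an expected error rate. The trial's being open is inferred from the absence of any described blinding and from the nature of the device. The change is worth making because it is cheap and the gap cannot be closed later.

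**What to change.** In Section 5, replace routine site-held envelopes with release of one assignment at a time from the central list that already exists, by web form or telephone, just before implantation. Before release the centre registers:

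- the patient number;
- the single- or dual-chamber stratum;
- completed eligibility, including the baseline troponin result where the four-week exclusion depends on it;
- the intended apical position.

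State that every registered patient counts as randomised.

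As back-up, or where central release is not feasible, use sequentially numbered opaque envelopes. Someone other than the implanter keeps them and marks each with patient number, date and time before opening. They are reconciled against the central list.

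Cost: a short wording change and one brief contact per patient, 290 in total. The downside is a small delay and dependence on availability, for example out of hours, which the back-up covers. No extra patients, visits or samples are needed, and no clinical criterion changes.

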#### Assessment of non-inferiority:

If the study fails to find statistical evidence for superiority of one method compared to the other, non-inferiority will be concluded, if the lower limit of the 95% confidence interval for the area under the ROC curve (AUC) is greater than 0.45. The AUC estimates the probability that the change in high-sensitivity troponin T plasma concentration is greater in a randomly selected patient treated with one method compared to a random sample from patients treated with the other method.

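### Intention to treat is the only analysis set the protocol names, and it is not reliably conservative for the non-inferiority fallback when lead-type cross-over is allowed

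*Protocol*

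**What the plan says.** **Cross-over.** Protocol section 5 (Study procedure) asks implanters to try to keep to the assigned lead type, but cross-overs "will be allowed on the basis of the individual judgement of the implanter". The analysis rule follows directly: "In case of cross-over, the primary endpoint will be evaluated on an intention-to-treat basis". No expected cross-over rate is given.

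**Groups.** Section 6 (Primary endpoint) compares the troponin increase "between patients receiving a passive fixation or an active fixation ventricular electrode". The null hypothesis in section 9 (Statistics) concerns "a randomly selected patient of the study cohort who received an active fixation ventricular pacemaker electrode" and the matching patient who received a passive lead. The paragraph on non-inferiority describes the AUC by the method each patient was treated with.

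**Fallback.** If superiority is not shown, "non-inferiority will be concluded, if the lower limit of the 95% confidence interval" for the AUC lies above 0.45. The paragraph does not say which analysis set applies. Intention to treat is the only set named anywhere in the protocol, but the protocol does not say that no other will be used.

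**The concern.** The superiority test and the non-inferiority fallback react differently to cross-over. Mixing lead types within the randomised arms tends to shrink a real difference. For superiority that costs power and is conservative. For non-inferiority it can hide a difference that lies at or beyond the margin.

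This matters because section 2 expects that the troponin increase "is not related to the use of an active or a passive fixation of the ventricular lead", a statement about the lead used, and the fallback is the only step that could support it.

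The wording is a smaller matter. Read literally, sections 6 and 9 place each crossed-over patient in the opposite group from the one that section 5 assigns.

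**Working it through.** **Inputs from the protocol (section 9).** Smallest relevant effect 0.60 (it "would determine the least difference that would be considered as clinically relevant"), two-sided 5% level, 80% power, 1:1 allocation, 262 patients (131 per group), non-inferiority limit 0.45.

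**Assumed.** The combined cross-over share x + y (x and y are the shares in the two arms) is taken as 0, 5, 10 and 20%.

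**1. The plan's own figure.** Noether's formula gives N = (1.960 + 0.842)² / [12 × 0.5 × 0.5 × (0.60 − 0.50)²] = 261.6, so 262. It reproduces.

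**2. Precision at 131 per group.** SE(AUC) = √[(131 + 131 + 1) / (12 × 131 × 131)] = 0.0357. The half-width of the 95% interval is 1.96 × 0.0357 = 0.070. The lower limit exceeds 0.45 only if the estimate exceeds 0.45 + 0.070 = 0.520.

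**3. Dilution.** Let t be the AUC between pure lead types, and let crossed-over patients respond like ordinary recipients of the other lead. Then

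AUC_ITT = (1−x)(1−y)t + xy(1−t) + 0.5[(1−x)y + x(1−y)] = 0.5 + (t − 0.5)(1 − x − y).

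**4. False non-inferiority at t = 0.45, one fixed direction.** The probability is 1 − Φ[(0.520 − AUC_ITT) / 0.0357].

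| x + y (assumed) | AUC_ITT | False non-inferiority |
|---|---|---|
| 0% | 0.4500 | 2.5% |
| 5% | 0.4525 | 2.9% |
| 10% | 0.4550 | 3.4% |
| 20% | 0.4600 | 4.6% |

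**5. Other true values.**
- At t = 0.50, dilution changes nothing. The bound is met 28.7% of the time at any cross-over share.
- At t = 0.55, 10% combined cross-over lowers the chance of meeting the bound from 79.9% to 75.8%. Counting only trials that first fail superiority, the figures are 51.2% and 51.6%, practically unchanged.

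**6. If crossed-over patients are not ordinary recipients.** As an illustration, take a normal model in which a second lead attempt adds 1 SD of damage and 10% cross over in one arm only, with AUC = P(A > P) and t = 0.45.
- Only passive patients cross: AUC_ITT is about 0.43. The bound is met with probability 1 − Φ[(0.520 − 0.43) / 0.0357], about 0.6%.
- Only active patients cross: AUC_ITT is about 0.48, and the probability is about 13%.

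The same 0.45 between pure lead types can therefore give a figure well below or well above 2.5%, depending on which arm crosses.

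**The case against.** **The cross-over rule already settles the groups.** Section 5 deals with exactly this case, and the wording in sections 6 and 9 can be read as shorthand for the randomised arms. This largely stands. A reader might infer that the primary comparison is undefined; the explicit rule in section 5 does not support that. The rewording is tidying.

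**Intention to treat may not be the only analysis.** A supportive per-protocol analysis could be in the statistical analysis plan, which is not at hand. This stands as a limit: the point is that the protocol names one set and ties no second set to the non-inferiority conclusion.

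**Cross-over does not manufacture non-inferiority.** A reader might infer that a pull towards 0.5 produces the expected answer. It does not. The estimate must exceed about 0.52, and an AUC of exactly 0.5 meets the bound less than a third of the time. The inflation arises only on the unfavourable side of 0.5.

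**The size is modest and the rates are assumed.** The protocol discourages cross-over, admits only centres experienced with both lead types, and excludes patients who need a particular fixation. At 5% combined cross-over the rise is 0.4 percentage points. This stands.

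**A per-protocol set has its own bias.** Cross-over is meant to rescue an implant that would otherwise fail, and section 6 itself relates troponin to procedure duration and number of mapping sites. Dropping these patients therefore selects on something plausibly tied to the outcome. This stands, and it is why the second set should supplement intention to treat and not replace it.

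**Conclusion.** The point holds as a cheap improvement. It is not an error that undermines the trial. Intention to treat is appropriate for the two-sided superiority test. For the fallback, a single intention-to-treat set cannot be relied on to be conservative: under simple dilution, false non-inferiority at a true AUC of 0.45 rises from 2.5% to between 2.9% and 4.6% over combined cross-over of 5% to 20%.

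These figures rest on assumed cross-over rates, 131 analysed patients per group, a normal approximation, one fixed direction of the AUC, and crossed-over patients who respond like ordinary recipients of the other lead. If that last assumption fails, the direction itself is open. The documents do not support any general statement that cross-over favours non-inferiority.

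**What to change.** 1. In sections 6 and 9, including the non-inferiority paragraph, word the endpoint, the null hypothesis and the AUC by randomised lead type.
2. Keep intention to treat for the superiority test.
3. Conclude non-inferiority only if the bound is met in both the intention-to-treat set and a per-protocol set, defined as patients whose final lead is of the randomised type.
4. Report the number and share of cross-overs by arm.

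**Cost.** Some wording and one further analysis of data already collected; no new patients or samples. The non-inferiority claim becomes slightly harder. For example, with an assumed 5% cross-over in each arm, about 124 per group remain (131 × 0.95), SE = √[249 / (12 × 124²)] = 0.0367, and the per-protocol estimate must exceed 0.45 + 1.96 × 0.0367 = 0.522 instead of 0.520. The selection bias of the per-protocol set should be acknowledged when the two results are read together.
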